**Fig. 1 f0005:**
[figure not shown]
In ART-Pro-1, patients with suspected clinically significant prostate cancer (csPCa) undergo MRI, with images interpreted independently by two expert radiologists. Radiologist 1 provides a research report using only biparametric MRI (bpMRI; no contrast) and then a second research report after reviewing the dynamic contrast-enhanced images (full multiparametric MRI [mpMRI]). Radiologist 2 provides a research report using bpMRI plus Restriction Spectrum Imaging restriction score (RSIrs). After both radiologists have submitted their research reports, they are given each other’s results. They may review all images and discuss the case, if useful. Radiologist 1 submits a final clinical report to the patient’s medical record to guide biopsy decisions. MRI = magnetic resonance imaging; w/ = with; w/o = without.

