### Secondary analyses

4.3

We will repeat statistical analyses above using an alternate definition of grade group (GG) ≥3 as true positives. GG 1 or benign will continue to be considered true negatives. We will also measure the detection of cancers of each GG (GG 1, 2, 3, or 4–5). GG 1 diagnoses will be considered undesirable overdiagnoses. Rates of overdiagnosis will be compared by McNemar’s test, as above.

The percentage of cases with diagnostic quality imaging as per PI-QUAL (as rated by reader 1 in ART-Pro-1) will be measured for each site and for the study, overall. The percentage of cases with significant distortion of DWI will be measured for each site and for the study, overall. The percentage of such cases where distortion correction was deemed diagnostically helpful will be measured for each site and for the study, overall.

Inter-reader reliability of PI-QUAL and bpMRI PI-RADS scores will be summarized using Cohen’s kappa, comparing ART-Pro-1 reader 1 with ART-Pro-1 reader 2.

We will calculate the percentage of csPCa detected on systemic biopsy only, targeted biopsy only, or both.

Radiologists estimate the probability of csPCa on biopsy for each patient and record this in the REDCap forms. We have previously reported objective estimates of probability of csPCa for RSIrs maximum in the prostate [35]. For ART-Pro patients who undergo biopsy, we will construct ROC curves for radiologists’ and RSIrs estimates, with 95% CIs via bootstrapping. We will compare discriminative performance for expert radiologists, nonexpert radiologists, and RSIrs. We will also visualize calibration for each of these via qq plots [43].

In ART-Pro-2, the overall performance of each approach (1–5) will also be compared by measuring the Akaike information criterion for each model.

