ART-Pro’s pragmatic design facilitates conduct of the study but also has some limitations. Biopsy decisions are made as per clinical routine and are not prescribed by the study, so biopsy may not be performed for some patients despite suspicious MRI. On the contrary, this reflects real-world practice. We expect that conducting the study at centers of excellence will mitigate the risk of nonstandard recommendations, and we have accounted for the possibility of patients declining a recommended biopsy in our power analysis. Clinical decisions for each patient are made based on the final recommendations of one radiologist (ART-Pro-1 reader 1). It is obviously not possible to have the same patient undergo two separate decisions, and our design allows for both reader 1 and reader 2 to influence the biopsy decision and biopsy targets. An alternative approach would be a randomized trial where patients are evaluated with only bpMRI, mpMRI, or RSIrs plus bpMRI. Such a randomized trial would suffer drawbacks of requiring many more patients (because of nonpaired statistical comparisons) and a considerable consenting effort that would inevitably slow accrual and introduce biases because some patient populations are less able to participate in research studies (eg, because of language barriers, complex wording of consent forms, burden of additional visits to complete consent, etc.). ART-Pro-2 has a retrospective design, meaning that the ART-Pro-2 radiologists do not influence biopsy decisions. They may, for example, identify additional lesions that were not targeted on biopsy. Given that each patient can have only one biopsy recommendation and the first biopsy procedure, we believe that the most ethical and most accurate approach is to have two expert radiologists at a center of excellence to influence biopsy recommendations that lead to the gold standard reference for the study’s primary outcome (presence of csPCa on biopsy).

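### Objective 9 compares experts, nonexperts and RSIrs only in biopsied men, a group chosen partly by the readers being compared, so the AUCs are distorted unequally in a direction the plan cannot know

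*Protocol article*

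**What the plan says.** Section 4.3 (Secondary analyses) sets out objective 9. The score is defined there: "Radiologists estimate the probability of csPCa on biopsy for each patient". The analysis set is fixed: "For ART-Pro patients who undergo biopsy, we will construct ROC curves". So is the comparison: "We will compare discriminative performance for expert radiologists, nonexpert radiologists, and RSIrs".

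Other sections describe how men come to be biopsied.

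- The Fig. 1 legend says reader 1's final clinical report goes to the patient's "medical record to guide biopsy decisions".
- Section 3.5.2 has reader 2 read bpMRI with RSIrs. Section 3.5.3 lets reader 1 revise after seeing that report.
- Section 5 (Summary) says "our design allows for both reader 1 and reader 2 to influence the biopsy decision and biopsy targets". It describes ART-Pro-2 as retrospective, "meaning that the ART-Pro-2 radiologists do not influence biopsy decisions".
- Section 3.5.4 leaves the biopsy decision to the medical team under clinical routine.

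Section 5 acknowledges that the study does not prescribe biopsy. Section 4.3 gives no correction or caution for the effect of this on the comparison.

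**The concern.** When a test helps to decide who is verified, restricting the analysis to verified patients truncates that test's score range. Tests that did not select are truncated only through their correlation with the selector. The three AUCs in Section 4.3 would come from the same men and still not be on an equal footing: ART-Pro-1 reader 1 selects directly, RSIrs selects in part through reader 2, and nonexperts do not select.

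Section 5 presents two questions as important: whether nonexperts can approach expert performance, and how RSIrs alone compares with expert reading. The planning AUCs in Section 4.1.2 are 0.767 for mpMRI and 0.747 for RSIrs, a difference of 0.020. A distortion of one to three hundredths is large enough to hide or reverse a difference of that size.

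**Working it through.** The plan gives no AUC, sample size or power for objective 9, so there is no figure to reproduce. The check asks how far AUCs in biopsied men depart from AUCs in all men.

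**Inputs from Section 4.1.2.** csPCa prevalence 30%; sensitivity 90%; specificity 40%; planning AUCs 0.767 (mpMRI) and 0.747 (RSIrs).

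**Assumed.** Biopsy rates, the correlation between scores within disease class, a nonexpert AUC of 0.70, and the weight of each reader in selection.

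**Model.** Binormal scores, with mean shift in csPCa d = √2 × Φ⁻¹(AUC).

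**Step 1: selection by reader 1 alone, equal true AUCs of 0.77.**

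MRI-positive share = 0.30 × 0.90 + 0.70 × (1 − 0.40) = 0.27 + 0.42 = 0.69. Assume biopsy in 95% of the top 69% of reader 1 scores and in 10% of the rest. Biopsied share = 0.69 × 0.95 + 0.31 × 0.10 = 0.6555 + 0.031 = 0.6865.

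| Correlation | Reader 1 AUC, biopsied | Other reader AUC, biopsied | Gap |
|---|---|---|---|
| 0.3 | 0.721 | 0.748 | 0.027 |
| 0.5 | 0.721 | 0.737 | 0.016 |
| 0.7 | 0.721 | 0.729 | 0.008 |

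The true gap is zero. If 30% of low scorers are biopsied, reader 1 is at about 0.738 and the other reader at 0.757, 0.748 and 0.744, so the gaps are 0.019, 0.010 and 0.006. With the planning AUCs and the 10% rate, the true lead of 0.020 for mpMRI becomes a deficit of under 0.01 at correlation 0.3, a lead of under 0.01 at 0.5, and is nearly preserved at 0.7.

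**Step 2: joint selection.** In the Step 1 setup at correlation 0.5, letting the second score share in selection cuts the gap from 0.016 to 0.008 (weights 2:1) and to about zero (1:1).

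**Step 3: all parties together.** A second simulation assumes 65% biopsied, selection on a continuous score plus noise, and true AUCs of 0.767 (both ART-Pro-1 readers and ART-Pro-2 experts), 0.747 (RSIrs) and 0.70 (nonexpert). AUC lost by restricting to biopsied men:

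| Selection | Correlation | Reader 1 | RSIrs | Nonexpert | ART-Pro-2 expert |
|---|---|---|---|---|---|
| Reader 1 alone | 0.5 | 0.059 | 0.042 | 0.049 | 0.040 |
| Readers 1 and 2, 2:1 | 0.5 | 0.075 | 0.061 | 0.062 | 0.052 |
| Readers 1 and 2, 1:1 | 0.5 | 0.072 | 0.065 | 0.064 | 0.053 |
| Readers 1 and 2, 2:1 | 0.7 | 0.070 | 0.068 | 0.078 | 0.060 |
| 2:1, csPCa missed more often where reader 1 scored low | 0.5 | 0.029 | 0.055 | 0.050 | 0.050 |

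The order changes. Reader 1 loses most in the first three rows, the nonexpert in the fourth and RSIrs in the fifth. When biopsy depended mainly on factors unrelated to the scores, every loss was about 0.01 and the differences nearly vanished.

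**Step 4: two candidate remedies in the Step 1 setup.** Weighting biopsied men by 1 / P(biopsy), with that probability known, returns both AUCs to within about 0.003 of the truth. Using all men and counting the unbiopsied as negative gives reader 1 an AUC of 0.82 against 0.77 to 0.80 for the other reader, a false expert advantage of about 0.02 to 0.05.

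**The case against.** A reader might infer that the expert AUC must fall most, so that the comparison favours nonexperts and RSIrs. The documents do not support that, for four reasons.

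- Selection is not by reader 1 alone. Reader 2's RSIrs-informed report and clinical routine also act, so RSIrs is itself partly a selector.
- A nonexpert with a lower true AUC can lose more than the expert when scores are highly correlated.
- Lesions named by the ART-Pro-1 readers set the biopsy targets, which helps those readers and can outweigh the selection effect.
- Section 4.3 does not say which experts it means. ART-Pro-2 has its own expert stratum (Section 3.7), which Section 4.2 uses as the reference level. Those experts do not select the sample either.

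All four points stand, and the direction cannot be asserted.

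The stakes are also limited. Table 1 does not mark objective 9 as key, and Section 4.3 attaches no margin or hypothesis to it. RSIrs against mpMRI, and the expertise strata, have their own analyses in Sections 4.1.1 and 4.2. At 500 patients the sampling SD of a paired AUC difference in this setup is about 0.03, so the distortion is no larger than about one SD. It is nevertheless a bias, and the planned bootstrap intervals would not reflect it.

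Finally, the score estimates csPCa on biopsy, so calibration in biopsied men is coherent. That is right for calibration, but it does not make the AUCs comparable. Details of a correction could be left to an unseen analysis plan, but the analysis set and the comparison are stated here.

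**Conclusion.** The point holds as a matter of differential partial verification. The objective 9 comparison uses a sample chosen partly by the ART-Pro-1 readers, which lowers AUCs by unequal amounts. The relative distortion is plausibly about 0.01 to 0.03 against reader 1 when reader 1 dominates selection and correlation is low to moderate. Its net sign is undetermined. These sizes rest on assumed biopsy rates, correlations and reader weights; only prevalence, sensitivity, specificity and the two planning AUCs come from the protocol. Priority is low to moderate.

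**What to change.** In Section 4.3:

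1. Keep the biopsied-only ROC curves and calibration plots, labelled descriptive.
2. Base the comparison of discrimination on biopsied men weighted by the inverse probability of biopsy. Model that probability from reader 1's final score, reader 2's score including RSIrs, PSA, age, prior biopsy and site. The reader scores are captured in the research reports, and the clinical items are available from the medical record.
3. State whether expert means ART-Pro-1 or ART-Pro-2 experts. ART-Pro-2 experts are the like-for-like comparator for nonexperts, because neither group selects the sample.
4. If the all-patient reference that counts unbiopsied men as negative is shown, present it only as a sensitivity analysis labelled as biased toward the selecting expert. Do not require the weighted result to agree with it.

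The cost is one weighted analysis, wider intervals and dependence on the biopsy model. In the Step 1 scenario only 500 × 0.31 × 0.10 = 15.5, about 16 men, would be low scorers with a biopsy, each weighted 1 / 0.10 = 10 against 1 / 0.95 = 1.05 for the rest. Weighting corrects selection into biopsy, provided the model captures what drives it. It does not correct cancers missed because of where the targets were placed, and the text should say so.

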### Objectives

2.2

The primary and secondary objectives are listed in Table 1.

**Table 1 t0005:** Study objectives

*Primary objectives*
1. Evaluate if bpMRI is noninferior to mpMRI among expert (ART-Pro-1) and nonexpert (ART-Pro-2) radiologists for the detection of GG ≥2 csPCa
*Secondary objectives*
1. Evaluate if RSIrs plus axial *T_2_*-weighted MRI is noninferior to mpMRI among expert and nonexpert radiologists for the detection of GG ≥2 csPCa a
2. Compare quantitative RSIrs (objective interpretation) with qualitative mpMRI (subjective radiologist interpretation) for the detection of GG ≥2 csPCa a
3. Evaluate bpMRI, mpMRI, and RSIrs for avoidance of unnecessary biopsies (ie, any biopsy resulting in no cancer or only GG 1) a
4. Evaluate bpMRI, mpMRI, and RSIrs for the detection of GG ≥3 cancer
5. Assess performance of the above MRI techniques for the detection of each: GG 1 (overdiagnosis), GG 2, GG 3, and GG 4–5
6. Evaluate the quality of scan images: a. Percentage of cases with diagnostic quality imaging as per PI-QUAL b. Percentage of cases with moderate or severe distortion i. Percentage of cases where distortion correction is useful
7. Evaluate csPCa detection by targeted vs systematic biopsy cores
8. Measure inter-reader reliability of bpMRI and mpMRI
9. Evaluate accuracy of radiologists’ and RSIrs-based estimates of overall probability of csPCa on biopsy
10. Assess influence of RSIrs on bpMRI interpretation

bpMRI = biparametric MRI; csPCa = clinically significant prostate cancer; GG = grade group; mpMRI = multiparametric MRI; MRI = magnetic resonance imaging; PI-QUAL = Prostate Imaging Quality; RSIrs = Restriction Spectrum Imaging restriction score.

a Key secondary objectives.

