#### Sample size calculations

4.1.2

All power calculations are conducted using software PASS 14.0.9 and R 4.3.1, unless otherwise indicated.

For testing the sensitivity, we expect the sensitivity to be 90% from the second test in each of the paired comparisons (reader 1 mpMRI), and assume a margin of 8% in defining noninferiority and an actual difference of 0%. We expect the percentage of probability of the first test giving a positive result while the second giving a negative result will be 5%. A sample size of 145 patients achieves at least 80% power at significance level 0.05. We plan to enroll 500 patients and expect that 30% will be diagnosed with csPCa, yielding 175 analyzable patients for the evaluation of sensitivity. Given the design of the trial, missing data are expected to be low (3%). Therefore, with the proposed sample size, we will have ample power in the above statistical tests.

For testing the specificity, we expect the specificity to be 40% from the second test in each of the paired comparisons, and assume a margin of 10% in defining noninferiority [42] and an actual difference of 0%. We expect the percentage of probability of the first test giving a negative result while the second giving a positive result will be 5%. Of 500 patients enrolled, 350 are expected to not be diagnosed with csPCa (either no biopsy due to low clinical/imaging risk or biopsy negative for csPCa), with a missing data rate of 3%. A sample size of 340 analyzable patients achieves at least 80% power at significance level 0.05.

For testing the noninferiority of the ROC curves associated with RSIrs and mpMRI, a preliminary study of 476 patients indicates that the AUC of the model with RSIrs is 0.747 (95% confidence interval [CI]: 0.7025–0.7884), while the AUC of the model with mpMRI is 0.767 (95% CI: 0.726–0.8085). With the proposed sample size, we will have at least 80% power in the noninferiority test with a margin of 8%. The power analysis is conducted with R 4.3.1 and package pROC.

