### Analyses for ART-Pro-2

4.2

Statistical analyses for ART-Pro-2 will be analogous to those described for ART-Pro-1. In ART-Pro-2, each radiologist will give sequential reports on each assigned patient case, that is, either (1) bpMRI and (2) mpMRI or (3) RSIrs plus T2W axial, (4) RSIrs plus bpMRI, and (5) RSIrs plus mpMRI. We will compare each approach (1 and 3–5) to mpMRI in an analogous manner to that in ART-Pro-1 using McNemar’s test and AUCs. These analyses will be performed within each stratum of ESUR radiologist expertise, testing for noninferiority compared with mpMRI PI-RADS for ESUR-defined experts (essentially a validation of ART-Pro-1), radiologists with basic prostate MRI proficiency, and novices. In terms of statistical power, each of these ART-Pro-2 subgroups will have the same statistical power as the primary and key secondary analyses of ART-Pro-1.

Additionally, we will estimate the effect of radiologist expertise for each approach (1–5) in linear mixed-effect models that utilize all the data from ART-Pro-2. Models will take the following form:csPCastatusscore+experience+(1|patient)+(1|radiologist)

Here, csPCa status is whether the patient was diagnosed with csPCa (binary), score is the PI-RADS or Likert score assigned, and experience is a categorical variable for ESUR/ESUI level of experience. Importance of radiologist experience within each approach (1–5) will be estimated by the parameter estimates for ESUR/ESUI basic proficiency and ESUR/ESUI novice levels, compared with a reference of ESUR/ESUI experts.

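### The qq plots planned in Section 4.3 cannot show calibration of csPCa probabilities against a binary biopsy result, so the calibration part of non-key secondary objective 9 is not answered as written

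*Protocol article*

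**What the plan says.** Table 1 of the protocol article (Section 2.2) lists secondary objective 9: "Evaluate accuracy of radiologists’ and RSIrs-based estimates of overall probability of csPCa on biopsy". It does not carry the mark for key secondary objectives, which only objectives 1 to 3 have.

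Section 4.3 describes the data and the analysis. For the readers: "Radiologists estimate the probability of csPCa on biopsy for each patient and record this in the REDCap forms". For the biomarker: "We have previously reported objective estimates of probability of csPCa for RSIrs maximum in the prostate". In patients who undergo biopsy, "we will construct ROC curves for radiologists’ and RSIrs estimates, with 95% CIs via bootstrapping", and discrimination is compared between expert radiologists, nonexpert radiologists and RSIrs. The calibration analysis is a single sentence with a literature citation: "We will also visualize calibration for each of these via qq plots".

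The outcome is dichotomous. Section 4.2 says so for its own model: "csPCa status is whether the patient was diagnosed with csPCa (binary" in the original parenthesis. The article names no other calibration method.

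**The concern.** Calibration is a conditional property: among patients told that their risk is about 30%, do about 30% have csPCa on biopsy? Answering that requires each prediction to be paired with the same patient's result. A qq plot sorts each variable separately and so discards the pairing. With an outcome that takes only the values 0 and 1, it also has no meaningful diagonal to compare with.

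What is at stake is the numerical correctness of the probabilities. The RSIrs probabilities come from earlier work, and whether they carry over to this cohort is a real question. So is whether readers' stated percentages run high or low. ROC curves do not address either, because they depend only on the ordering of the predictions. A predictor could rank patients well and still be systematically too high or too low, and the analyses named would not measure that.

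**Working it through.** The plan states no sample size, power or numerical target for this analysis, so there is no figure to reproduce. The check is of the method.

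**Inputs.** From the article: predicted probabilities per patient, a binary outcome, and a csPCa frequency of 30% among those enrolled (Section 4.1.2: "We plan to enroll 500 patients and expect that 30% will be diagnosed with csPCa"). The frequency among biopsied patients is not given and may differ; 30% is used only for illustration. Assumed: predictions p drawn from a Beta(1.2, 2.8) distribution, with mean 1.2/(1.2 + 2.8) = 0.30, and outcome y drawn as Bernoulli(p). These predictions are perfectly calibrated by construction. There were 200,000 simulated patients, so that sampling noise is negligible.

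**Step 1: the literal qq plot.** The points are (quantile of p, quantile of y) at the same percentile. For an outcome with frequency π, the quantile of y is 0 below percentile 1 − π and 1 above it. With π = 0.30 the jump is at 1 − 0.30 = 0.70.

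| Percentile | Quantile of p | Quantile of y |
|---|---|---|
| 5 | 0.03 | 0 |
| 65 | 0.36 | 0 |
| 70 | 0.40 | 1 |
| 95 | 0.69 | 1 |

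This is a step, although calibration is perfect. A different frequency among biopsied patients moves the jump but leaves it a step.

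**Step 2: other things a qq plot could compare.** Predicted risk in cases against non-cases also lies off the diagonal under perfect calibration (medians 0.43 and 0.20). It displays separation, which the ROC curve already covers. Reader probabilities against RSIrs probabilities would not involve the biopsy result at all.

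**Step 3: what a calibration plot shows.** In the same data, grouped by decile of p, mean predicted against observed proportion was 0.03/0.03, 0.24/0.23, 0.54/0.54 and 0.71/0.70 in the first, fifth, ninth and tenth deciles. The logistic calibration slope was 0.996. The plot follows the diagonal, as it should.

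**Step 4: the error that the ROC curve misses.** Halve every probability. Ranks are unchanged, so the ROC curve and its area are exactly the same. The ninth decile now has predicted 0.54/2 = 0.27 against observed 0.54, and the overall mean is 0.30/2 = 0.15 against 0.30. A calibration plot shows a twofold understatement at every level. The literal qq plot remains a step with its points moved left, and offers no reference line to say which of the two sets is right.

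**The case against.** The strongest reply is that the term may be loose wording. The sentence states its purpose and cites a source that is not available here. Binning predictions by quantile and plotting observed against expected risk is a proper calibration plot, and an article need not give axes and construction. That stands as a possibility. It does not remove the point: the text then names the wrong plot, and nothing else in the article supplies the right one.

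A second reply is that a literal qq plot is not wholly empty. The position of the jump gives the overall csPCa frequency and the horizontal axis gives the spread of predictions, so a determined reader could compare the two averages. That also stands, but it gives no observed frequency at any level of predicted risk.

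A reader might infer that the plot could make a poor or uninformative predictor look acceptable. The documents do not support that. A step off the diagonal makes no predictor look well calibrated, and a predictor unrelated to outcome would be exposed by the ROC curves planned in the same paragraph. The risk is an uninformative figure and an unanswered question, not false reassurance.

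It is also fair to say that the analysis is descriptive, that objective 9 speaks of accuracy in general, and that its discrimination part is sound. This limits the weight of the point.

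**Conclusion.** The point holds in limited form. Read literally, the only calibration tool named cannot compare predicted risk with observed csPCa frequency for a binary outcome. The ROC curves cannot fill the gap, because they ignore systematic over- or understatement. The calibration part of secondary objective 9 is therefore not answered as written.

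The consequence is confined to that non-key, descriptive objective. No test, margin, sample size, primary or key secondary conclusion depends on it. The probabilities and biopsy results are collected in any case, so nothing is lost if the wording is corrected before analysis.

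That the plot is a step follows from the 0/1 outcome and does not depend on the simulation's assumptions; the decile figures do depend on the assumed Beta distribution and 30% frequency. The conclusion assumes the term carries its usual meaning. If a quantile-binned plot was intended, what remains is a wrong term to correct.

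**What to change.** In Section 4.3, replace the qq plots with calibration plots: observed csPCa proportion, binned or smoothed, against predicted probability, in patients who had a biopsy. Provide them for every group whose estimates are evaluated: ART-Pro-1 readers 1 and 2 (Sections 3.5.1 and 3.5.2), ART-Pro-2 expert, basic and novice readers (Section 3.7), and RSIrs.

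Calibration intercept and slope may be added with bootstrap 95% confidence intervals. This is optional, since the plan promises only a visual check. Intervals would help at this trial's size: single simulated samples of perfectly calibrated predictions gave slopes of 1.166 at n = 300 and 1.046 at n = 500. The bootstrap should resample patients, so that repeated reads of one case stay together; in ART-Pro-2 each case is read by six radiologists.

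The cost is a changed sentence and a small amount of extra analysis code. No new data are needed, and the sample size and primary analysis do not change.

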### MRI interpretation in ART-Pro-2

3.7

ART-Pro-2 will be conducted retrospectively and will not impact patient care. Radiologists will be categorized by level of experience for prostate MRI based on the joint European Society of Urogenital Radiologists (ESUR) and the EAU Section of Urological Imaging (ESUI) criteria: novice prostate radiologists defined as having read <400 cases, basic prostate radiologists defined as having read ≥400 and <1000 cases, and expert prostate radiologists defined as having read ≥1000 cases [11]. The design of ART-Pro-2 in evaluating nonexpert readers retrospectively allows for “locking” of reader experience level, whereas if evaluated over the ART-Pro-1 trial period, readers could change (by criteria) from being novice to basic and/or expert. Each radiologist will be provided a list of 100 patient cases to review, 50 with mpMRI and 50 with RSIrs plus mpMRI. Case lists will be generated as random permutations of cases while requiring that (1) no radiologist be assigned cases from the institution where he/she works (to ensure that the radiologist has not seen the cases before), (2) each patient case is assigned to at least three radiologists as mpMRI (one from each of the experience levels), and (3) each patient case is assigned to at least three (different) radiologists (one from each of the experience levels) as RSIrs plus mpMRI. Thus, each patient case will be reviewed by six radiologists (two from each of the experience levels). Image sets will be provided as sessions using the MIM Zero Footprint platform (MIM Software, Cleveland, OH, USA) to facilitate individual work lists and presentation of image subsets.

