#### Statistical analysis plan for primary and key secondary objectives

4.1.1

An exploratory data analysis will be conducted, and visualization tools, including the scatterplot, boxplot, and histogram, will be used to examine the data and potential missingness [39]. For all tests below, the significance level of 0.05 will be used in the statistical testing. All analyses will be conducted using software R 4.3.1.

For examining the noninferiority of bpMRI versus mpMRI for the detection of csPCa, we will conduct one-sided noninferiority tests of correlated proportions, to examine the sensitivity and specificity of the following paired readings: reader 1 bpMRI versus reader 1 mpMRI and reader 2 bpMRI versus reader 1 mpMRI. For both paired comparisons, the outcome of each reading for each patient is the binary result of positive or negative MRI. A McNemar's test will be used to test the null hypothesis that the differences in the probabilities (% of second test minus % of the first test) of positive MRI (for testing on sensitivity) and negative MRI (for testing on specificity) from the two readings in the paired comparison are larger than the predetermined noninferiority margins [40]. The *p* values will be reported for all tests.

For examining the noninferiority of RSIrs versus mpMRI, we will compare the areas under the receiver operating characteristic (ROC) curve (AUCs) of using RSIrs (continuous variable) to predict the binary outcome of csPCa versus using mpMRI (ordinal categorical variable; treat like continuous variable) to predict the outcome [41]. A noninferiority test will be conducted to compare the two ROC curves associated with the two predictors at significance level 0.05.

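### The AIC comparison of the five ART-Pro-2 reading approaches cannot rank their accuracy: with the patient intercept the model is degenerate, and without it the AIC gaps have no calibrated error rate

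*Protocol article*

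**What the plan says.** Section 4.2 (Analyses for ART-Pro-2) defines five approaches: (1) bpMRI, (2) mpMRI, (3) RSIrs plus axial T2W, (4) RSIrs plus bpMRI and (5) RSIrs plus mpMRI. It sets two kinds of analysis.

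- **Formal comparisons.** "We will compare each approach (1 and 3–5) to mpMRI in an analogous manner to that in ART-Pro-1". These use McNemar's test and AUCs within each expertise stratum. Section 4.1.1 fixes their error rate: "the significance level of 0.05 will be used in the statistical testing".
- **Models.** The effect of expertise is estimated for each approach "in linear mixed-effect models that utilize all the data from ART-Pro-2". The printed form is "csPCastatusscore+experience+(1|patient)+(1|radiologist" (the tilde and closing bracket are lost in the text). The outcome is defined per patient: "csPCa status is whether the patient was diagnosed with csPCa (binary". On the predictor side, "score is the PI-RADS or Likert score assigned, and experience is a categorical variable for ESUR/ESUI level of experience".

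Section 4.3 (Secondary analyses) then adds that "the overall performance of each approach (1–5) will also be compared by measuring the Akaike information criterion for each model". It gives no threshold and no rule for declaring one approach better.

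Section 3.7 sets the reads. Each radiologist receives 100 cases, 50 on the mpMRI list and 50 on the RSIrs list. Each case goes to three radiologists on the mpMRI list, and "each patient case is assigned to at least three (different) radiologists (one from each of the experience levels) as RSIrs plus mpMRI".

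**The concern.** AIC trades fit against the number of parameters. Here every model has the same terms, so the penalty is identical and cancels. What remains is a difference of log-likelihoods between non-nested models that differ only in which scores enter.

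Two features of the design then matter. The outcome has one value per patient but appears on three rows per approach. The model also contains a patient intercept, which is free to absorb an outcome that never varies within a patient.

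At stake is the only stated comparison that sets all five approaches side by side on overall performance. The Summary links RSIrs plus axial T2W (approach 3) to a possible very short examination. An AIC ranking could be quoted for or against that approach without evidence behind it.

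**Working it through.** The plan gives no figure for the AIC comparison, so there is none to reproduce.

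**Inputs from the article.** 500 patients and 30% csPCa (4.1.2). Six reads per patient, three per list (3.7), so 500 × 3 = 1500 reads per approach and 500 × 6 / 100 = 30 radiologists. The mpMRI AUC is 0.767 (4.1.2); the check below used 0.755 for every approach, so all approaches are equally accurate by construction.

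**Step 1: the model as written.** Let θ be the patient SD divided by the residual SD. With N = 500 patients, n = 1500 reads, and the radiologist intercept left out, the maximum-likelihood AIC at a given θ is

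AIC(θ) = n[1 + ln(2π·RSS(θ)/n)] + N·ln(1 + 3θ²) + 12.

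Status is constant within patient. With score and experience effects set to zero, RSS(θ) = 3·Σ(y − ȳ)² / (1 + 3θ²). Hence

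AIC(θ) ≤ C − 1500·ln(1 + 3θ²) + 500·ln(1 + 3θ²) = C − 1000·ln(1 + 3θ²),

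where C does not involve the score. This falls without limit as θ grows, and the bound is the same for every approach. Adding the radiologist intercept does not help: setting its variance to zero returns the same likelihood.

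One simulated data set, approaches 1, 2 and 3:

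| θ | AIC | score coefficient |
|---|---|---|
| 0 | 1715 / 1712 / 1705 | about 0.14 |
| 1 | 462 / 463 / 461 | about 0.07 |
| 3 | −1389 / −1388 / −1388 | about 0.013 |
| 10 | −3743 for all three | about 0.001 |
| 1000 | −12948 for all three | 0 |

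Check against the formula: from θ = 100 (AIC −8343.1) to θ = 1000 (−12948.2) the drop is 4605.1, and 1000·ln(3000001/30001) = 4605.1.

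Over 300 equal-accuracy trials per θ, the share with an AIC gap above 2 was as follows. Same readers means approach 1 v 2. Different readers means approaches from the two lists, read by different radiologists for a given patient.

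| θ | same readers | different readers |
|---|---|---|
| 0 | 91% | 95% |
| 1 | 80% | 91% |
| 3 | 30% | 53% |
| 10 and 100 | 0% | 0% |

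The gap therefore depends on θ, and the likelihood always favours a larger θ.

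**Step 2: a logistic mixed version.** AIC kept falling over the range of patient SD tried (in one data set, 1308.0 at SD 1 and 656.3 at SD 20 for approach 1). The share with a gap above 2, same/different readers, was 62%/78% at SD 5 (60 trials) and about 12%/32% at SD 20 (25 trials). Changing the link does not give a stable comparison.

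**Step 3: no random effects.** Two separate simulations of equally accurate approaches, with 1500 reads each and linear and logistic fits, gave these ranges:

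| Gap | same readers | different readers |
|---|---|---|
| above 2 | 85-94% | 93-97% |
| above 10 | 39-72% | 68-81% |

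With five equal approaches, the best led the second by more than 2 in 82-90% of trials. With one read per patient (500 reads), a gap above 2 still occurred in 77-90% (same readers) and 88-93% (different readers), so the triple counting enlarges the problem but does not create it.

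**Step 4: benchmark.** A paired AUC test clustered on patient, two-sided 0.05, 400 trials per setting, rejected in 5.8-8.3% of equal-accuracy trials. That is somewhat above nominal; the test accounted for patients but not for readers.

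**The case against.** The strongest reply is that the AIC line is descriptive. It comes last in the secondary analyses, is introduced as an addition, and carries no decision rule. Approaches 1, 3, 4 and 5 are already tested against mpMRI by McNemar's test and AUC. AIC is used to compare non-nested models of one outcome, and it has no type I error rate by nature. How a supplementary statistic is reported may be left to an analysis plan that is not shown.

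Much of this stands, and it rules out several stronger readings that a reader might infer.

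- *That the planned analysis would name a better approach in most trials of equal approaches.* The high percentages come from models without random effects. In the written linear model the gaps shrink to nothing as θ rises.
- *That the problem is the same however the random effects are handled.* The lack of an error rate is; the percentages are not.
- *That the plan declares the lowest AIC the winner.* It does not. Any ranked continuous statistic has a best value, including an AUC point estimate, so that alone is no evidence against AIC.
- *That the two lists are read by different radiologists.* This holds only within a patient; every radiologist reads both lists.
- *That conclusions on bpMRI or RSIrs against mpMRI rest on AIC.* They do not.

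What the reply does not answer is that the article itself fixes both the model and the use of its AIC to compare performance. No later reporting detail makes that AIC informative about accuracy.

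**Conclusion.** The point holds, for a supplementary secondary analysis. Fitted as written, the linear model has an unbounded likelihood, and its AIC says nothing about the approaches; this is algebra and rests on no simulation assumption. Fitted without the patient intercept, the AIC gap exceeds 2 in about 85-97% of trials with no true difference, so it cannot separate a real difference from sampling.

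Those percentages rest on assumptions outside the article: 5-point scores, equal accuracy, a patient share of variance of 0.2-0.7, a reader share of 0.05 and a same-reader residual correlation of 0.5-0.95 in one simulation, and a comparable latent-score set-up in the other. The cut-offs 2 and 10 are illustrative. How much the shared reader pool would change the different-reader figures was not quantified.

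Pairs that do not involve mpMRI, such as bpMRI against RSIrs plus bpMRI, have no other stated comparison by approach, which is why the sentence is worth correcting.

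**What to change.** In section 4.3, replace the AIC sentence. For each pair of approaches, report the difference in AUC (or Brier score) computed from the scores, with a 95% confidence interval from a method that keeps all reads of a patient together and accounts for readers: a two-way patient-and-reader bootstrap or a multireader-multicase method. Claim a difference only when the interval excludes zero.

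The cost is one sentence and one further analysis run on data already collected; the same section already plans bootstrap intervals for ROC curves. The small downside is that fewer approaches will be separable.
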